## Abstract

**Background:**

Innovative disease management strategies have significantly improved clinical outcomes in inflammatory arthritis (IA). Although more than 80% of patients achieve low disease activity (LDA), the disease continues to exert a considerable impact on patients’ lives. For these patients with IA, a lifestyle intervention program may add value by reducing inflammatory activity, potentially alleviating the disease burden and the risk of a flare.

**Objective:**

This study aimed to compare 12-month disease management outcomes between patients with rheumatoid arthritis (RA) and psoriatic arthritis (PsA) with LDA who follow an online, interactive lifestyle intervention program (Leef! met Reuma) and those who receive general nutrition recommendations offered as part of usual care.

**Methods:**

The Healthy Living in Inflammatory Arthritis (HELIA) trial is an open-label, randomized controlled clinical trial with the aim of enrolling 200 adult patients diagnosed with RA or PsA according to the American College of Rheumatology or European Alliance of Associations for Rheumatology 2010 criteria, or Classification for Psoriatic Arthritis criteria, respectively. Other inclusion criteria were (1) having LDA defined as Disease Activity Score ≥2.6 and <3.5 or Disease Activity in Psoriatic Arthritis >4 and <16 and (2) stable disease-modifying antirheumatic drug dosages for ≥6 months prior to randomization. Patients are randomized into a lifestyle intervention or general nutrition recommendations using a 1:1 allocation ratio. The lifestyle intervention program consists of a 6-month intensive part, followed by an 18-month aftercare period. During the intensive part, there were 5 online Zoom (Zoom Communications Inc) meetings and 7 coaching sessions. The program focuses on 4 pillars, namely nutrition, exercise, relaxation, and sleep. The prescribed diet resembles the Mediterranean diet, with an emphasis on unprocessed foods. The general nutrition recommendations are based on the Dutch food-based dietary guidelines. The primary objective is the proportional difference in Disease Activity Score and Disease Activity in Psoriatic Arthritis remission and/or successful tapering of disease-modifying antirheumatic drug treatment after 12 months of follow-up. Meeting either criterion is sufficient to qualify for the primary outcome. Additionally, a cost-effectiveness analysis will be conducted using the incremental cost-effectiveness ratio as the outcome. Other secondary objectives include health risk and clinical and patient-reported outcomes over time and at specific time points. Primary and secondary outcomes are analyzed according to an intention-to-treat principle.

**Results:**

The trial was registered in the ISRCTN (International Standard Randomised Controlled Trial Number) registry retrospectively after recruitment had begun, due to administrative issues. The authors acknowledge this deviation.

**Conclusions:**

A randomized controlled trial is performed to compare the effectiveness of an online, interactive lifestyle intervention program and general nutrition recommendations in patients with IA with LDA from a clinical, patient, and societal point of view. If the intervention is proven effective, it can be applied as a complementary option to current treatment approaches.

## Introduction

Clinical outcomes of patients with an inflammatory arthritis (IA), including rheumatoid arthritis (RA) and psoriatic arthritis (PsA), have improved enormously due to further development of disease management strategies [1]. As a result, >80% of the patients with an IA reach low disease activity (LDA) [1]. Nevertheless, the disease still continues to exert a considerable impact on patients’ lives, manifesting as persistent fatigue, pain, and morning stiffness [2]. This residual disease activity is less in patients with IA who are in remission. Unfortunately, remission occurs less often and is not always achievable with current disease-modifying antirheumatic drug (DMARD) treatment. Irrespective of the residual disease activity, patients with IA frequently express a desire to taper their medication, even with the risk of a disease flare, due to concerns about side effects (ie, infections). For these patients, a lifestyle intervention program might be of added value, as increasing evidence suggests that lifestyle factors interfere with inflammatory activity and, consequently, a lifestyle intervention aimed at reducing inflammatory activity might lessen disease burden and the risk of disease flares [3-6].

Furthermore, previous research showed that patients with IA can undertake steps to improve their dietary quality as a possible strategy to manage arthritis [7]. Other studies also showed that certain diets, such as the Mediterranean diet, may add value for patients with IA [8-12]. Additional lifestyle factors, such as physical activity, sleep, and stress, also influence the course of IA [13-15]. Some researchers even state that lifestyle interventions should be the basis of IA treatment [15].

A recent lifestyle intervention trial, called “Plants for Joints,” in patients with RA and osteoarthritis showed promising outcomes. Patients with RA showed significant improvements in metabolic status and C-reactive protein (CRP) levels (median change −1.2, IQR –2.1 to –0.3). Disease activity also improved, demonstrated by a significantly lower Disease Activity Score (DAS28) after 1 year of the intervention, with sustainment of this improvement in the second year of follow-up (mean DAS28 change from baseline −0.9, SD –1.2 to –0.6). Consequently, half of the patients with RA were able to taper their medication, an effect that also persisted during the entire follow-up [16,17].

In line with this, Voeding Leeft, a nonprofit organization, developed a lifestyle program for patients with a rheumatic disease (Leef! met Reuma). This lifestyle intervention is aimed at achieving a lasting behavioral change (based on the I-Change model) [18]. Voeding Leeft already offers other lifestyle programs, including Reverse Diabetes 2 Now, with proven efficacy [19]. A pilot study that investigated the effect of Leef! met Reuma showed promising results, specifically improvement of health risks such as a reduction in weight, BMI, and waist circumference, and a reduction in disease burden [20]. However, the aforementioned outcomes were based on self-reported data, patients were not randomized, and there were no data on disease activity in patients with IA.

Therefore, the primary objective of this study is to compare 12-month disease management outcomes between patients with RA and PsA with LDA who follow an online, interactive lifestyle intervention program (Leef! met Reuma) and those who receive general nutrition recommendations, by measuring the proportional difference in DAS28 and Disease Activity in Psoriatic Arthritis (DAPSA) remission and/or successful tapering of DMARD treatment. Meeting either criterion is sufficient to qualify for the primary outcome.

Secondary objectives are:

To evaluate the cost-effectiveness of the online lifestyle intervention program versus general nutrition recommendations, by using the incremental cost-effectiveness ratio (ICER) as the outcome, which is the ratio of the difference in costs to incremental benefits between both interventions.To compare health risk (weight, BMI, and waist circumference) between the lifestyle intervention program and general nutrition recommendations.To compare disease impact between an online, interactive lifestyle intervention program and general nutrition recommendations offered as part of usual care in patients with IA with LDA by assessing the difference in patient-reported outcomes (PROs), namely general health (GH), pain, morning stiffness, fatigue, functional ability, and quality of life, over time and specific time points.

## Methods

### Trial Design and Setting

The Healthy Living in Inflammatory Arthritis (HELIA) trial is an open-label, randomized controlled trial and takes place at the Erasmus MC, an academic hospital in Rotterdam, The Netherlands.

### Recruitment and Eligibility Criteria

#### Recruitment

Patients with RA or PsA who have reached LDA but still experience disease-related problems are asked by their treating rheumatologist to participate in the study. If they are interested in participating in the trial, they will be given the patient information folder. Once patients have given their consent after a reflection period of ≥48 hours, the research nurse (RN) will check whether the patient meets the inclusion criteria. If trial participation is declined, then patients will be treated according to the insight of the treating rheumatologist using current treatment recommendations as a guideline. By signing the informed consent, patients authorize the retrieval of necessary data from their medical records for the study.

#### Inclusion Criteria

The inclusion criteria for this study are as follows:

1. Diagnosed with RA or PsA according to the American College of Rheumatology or European Alliance of Associations for Rheumatology (EULAR) 2010 criteria or Classification for Psoriatic Arthritis criteria, respectively [21,22].2. LDA, defined as DAS28 ≥2.6 and <3.5 or DAPSA >4 and <16 [23,24].3. Stable DMARD dosage and oral prednisone (or equivalent) at a dose ≤7.5 mg for ≥6 months prior to randomization.4. Age ≥18 years.

#### Exclusion Criteria

The exclusion criteria for this study are as follows:

1. Vegan diet or lifestyle, or following a specific (medical) diet.2. History of bariatric surgery.3. Pregnant or nursing (lactating) women.4. Underlying metabolic, hematologic, renal, hepatic, pulmonary, neurologic, endocrine, cardiac, infectious, or gastrointestinal conditions that, in the opinion of the investigator, place the patient at unacceptable risk for participation in a lifestyle intervention program.5. Unable to understand, speak, and write in Dutch.

### Randomization and Blinding

Patients are randomized with a 1:1 allocation ratio into the intervention group (participating in the online, interactive lifestyle intervention program) or the control group (receiving general nutrition recommendations), using ALEA clinical software (ALEA Clinical B.V.). The allocation sequence was balanced for diagnosis (RA or PsA). Patients, treating physicians, RNs, and researchers will know to which group patients are randomized. The principal investigator will generate the allocation sequence and will assign participants to interventions using ALEA clinical software. RNs will enroll participants and do not have access to the randomization sequence. During statistical analysis, treatment allocation will remain concealed through the use of masked group labels.

### Interventions

#### Online, Interactive Lifestyle Intervention Program

The online, interactive lifestyle intervention program (Leef! met Reuma) consists of a 6-month, intensive part followed by an 18-month online aftercare period. The online program focuses on 4 pillars, namely nutrition, exercise, relaxation, and sleep. The general principles for each pillar are summarized in Table 1. All principles are explained in more detail during the online plenary sessions (the why and how behind them) through Zoom (Zoom Communications Inc), which can be accessed via a standard web browser. Participants are given tools to implement a healthier lifestyle and to increase their health skills. They are encouraged to implement those changes in ways that fit their daily life. The lifestyle intervention aims for lasting behavior changes (based on the I-Change model) [18]. The guidance team consists of a coach, a dietitian, a program coordinator, and experts on sleep, relaxation, and physical activity. The nutritional advice and diet recommended throughout the course are based on the Dutch Health Council guidelines and existing scientific literature. The diet that is prescribed is comparable to the Mediterranean diet, with an emphasis on unprocessed foods (especially vegetables) and 3 meals a day. Alcohol is excluded from the diet.

Each month, a different pillar is highlighted. Throughout the month, participants are assigned 10 days of daily tasks focused on physical activity, relaxation, or sleep (with the option to extend this period to 28 d). Figure 1 provides a schematic overview of the intervention.

**Table 1. T1:** General principles of Leef! met Reuma.

Pillar	Principles
Nutrition^a^	Eat unprocessed foods and vary in the foods you eat. Eat mostly plant-based. Pay attention to dietary quality and not solely energy content.
Physical activity	Strive to increase your heart rate with moderate-intense physical activity for at least 15‐30 min a day. Implement more physical activity during the day; all physical activity counts. Vary in the type of physical activity you do and find a type of physical activity that suits you and that you can enjoy.
Relaxation	Learn to notice when you are stressed and what causes you to be stressed. Find your personal way to implement relaxation. Control your breathing.
Sleep	Pay special attention to sleep quality and not only to the amount of sleep. Develop your own personal, effective sleep hygiene.

a Comparable to the Mediterranean diet.

**Figure 1. F1:**
[figure not shown]
Schematic overview intervention (Leef! met Reuma).

There are 5 online plenary sessions lasting 3 to 4 hours for all participants (50 per group), and each session focuses on 1‐2 pillars. The online sessions start with a presentation with in-depth information about the specific pillar, and throughout the presentation, participants can ask questions. After that, the group is divided into several smaller online coaching groups. In these groups, the coach explains how to implement specific changes into participants’ lifestyles. During these 1-hour coaching sessions, the progress that participants have made will be discussed, but also obstacles, experiences, or situations that participants have encountered. Tips are given to help them stay motivated and keep the lifestyle behavioral changes they have made. One example is that participants will learn how to develop their own recipes according to the nutrition principles of the lifestyle program.

After the first 6 months, participants can participate in facultative sessions to stay motivated and foster the healthier habits they have learned during the intensive part of the program. These facultative sessions are similar to the coaching sessions but also include a recap of the knowledge gained during the first 6 months of the program. A facultative session is organized every 9 weeks. The total duration of these plenary, coaching, and facultative sessions is 16, 7, and 10 hours, respectively.

Throughout the entire program, participants can access the Voeding Leeft online platform to stimulate the implementation of healthier habits. At this platform, there are recipes for 30 days, and participants can also find more background information about all 4 pillars, ask questions (directed at the program coordinator, nutritionist, coach, or peers), chat with other participants to share their experiences and/or track their progress to ensure the implementation of a more lasting lifestyle behavior change.

Noteworthy is the fact that there will be no information exchange between the treating rheumatologist and the organization of the online, interactive lifestyle intervention program. However, for this trial, Voeding Leeft will record whether participants attend the plenary and coaching sessions and track their activity on the online platform.

#### General Nutrition Recommendations

The general nutrition recommendations are based on The Wheel of Five of the Dutch food-based dietary guidelines [25]. These recommendations are given in consultation with the RN. The general nutrition recommendation shows how much of what we eat should come from food groups to achieve a healthy, balanced diet. An overview of these recommendations is shown in Textbox 1. All patients at Erasmus MC’s rheumatology outpatient clinic receive this information as part of usual care. Therefore, this is chosen as a comparator for the intervention.

Textbox 1.General nutrition recommendations for the control group, based on The Wheel of Five of the Dutch food-based dietary guidelines.Eat at least 5 portions of a variety of fruit and vegetables a day.They should make up over a third of the food we eat each day.Choose from fresh, frozen, tinned, dried, or juiced.Fruit juice and smoothies should be limited to no more than a combined total of 150 mL a day.Basic meals based on potatoes, bread, rice, pasta, or other starchy carbohydrates.Starchy food should make up just over a third of the food we eat.Choose higher-fiber whole-grain varieties, such as whole-wheat pasta and brown rice, or simply leave skins on potatoes.Have some dairy or dairy alternatives (ie, soya drinks or yogurts).Eat some beans, pulses, fish, eggs, meat, and other protein.Aim for at least 2 portions of fish every week, 1 of which should be oily, such as salmon or mackerel.Choose unsaturated oils and spreads and eat them in small amounts.Eat foods high in fat, salt, and sugar less often and in small amounts.Drink plenty of fluids—the government recommends 6 to 8 cups or glasses a day.Water, lower-fat milk, and lower-sugar or sugar-free drinks, including tea and coffee, all count.

### Strategies to Improve Adherence to Interventions

Patients have a personal responsibility for the implementation of the online lifestyle intervention program theory or general nutrition recommendations into their own lives. All food products are available at the local grocery store or butcher, and participants should buy them at their own expense. To measure adherence to the lifestyle program, a questionnaire is included to assess diet compliance. In addition, a sensitivity analysis will be performed on patients who have ≥5% weight loss after the intensive part of the lifestyle intervention program because we assume that this weight loss is associated with program adherence.

### Relevant Concomitant Care Permitted or Prohibited During the Trial

The use of DMARDs, oral prednisone (or equivalent) at a dose ≤7.5 mg as cointerventions are permitted if participants have received a stable dose for ≥6 months prior to randomization. Tapering, continuation, or intensification of treatment during the study is left to the discretion of the treating rheumatologist in consultation with the patient, using current treatment recommendations as a guideline. There are no specifically excluded concomitant medications.

Escape medication is defined as any new therapeutic intervention or a significant change to ongoing therapy made because a participant is experiencing worsening or exacerbation of their disease. Only the following prespecified escape medications are allowed:

A total of 80 mg triamcinolone acetonide or 120 mg methylprednisolone intramuscular (maximum of 1 per 3 mo).Triamcinolone acetonide intra-articular ≤40 mg (maximum of 2 per 3 mo).Nonsteroidal anti-inflammatory drugs.

### Criteria for Discontinuing or Modifying Allocated Interventions

Criteria for discontinuing are as follows:

Pregnancy.Ineligibility (either arising during the trial or retrospectively having been overlooked at screening).An adverse event (AE), which requires discontinuation of the lifestyle intervention or results in the inability to continue to comply with trial procedures.Disease progression, which requires discontinuation of the lifestyle intervention or results in the inability to continue to comply with trial procedures.Withdrawal of consent.Loss to follow-up.

### AEs

The health risk of the intervention is expected to be low. AEs are defined as any undesirable experience occurring to a participant during the study, whether or not considered related to the intervention. All AEs reported spontaneously by the participant or observed by the investigator or research staff will be recorded. AEs of special interest during the study will be collected at each study visit through patient questionnaires and/or physician reports. Such AEs include the following:

Patient reported: infections (most common: [upper] airway), indigestion, diarrhea, and headache.Physician reported: infections, abnormal blood counts, abnormal liver function tests, decrease in kidney function, and increased cholesterol levels.

A serious adverse event (SAE) is any untoward medical occurrence or effect that:

results in death; oris life-threatening (at the time of the event); orrequires hospitalization or prolongation of existing inpatients’ hospitalization; orresults in persistent or significant disability or incapacity; oris a congenital anomaly or birth defect; orany other important medical event that did not result in any of the outcomes listed above due to medical or surgical intervention but could have been based upon appropriate judgment by the investigator.

An elective hospital admission will not be considered as an SAE. The investigator will report all SAEs that occur during the 2-year follow-up period to the sponsor without undue delay after obtaining knowledge of the events.

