### Participant Timeline

Patients will be assessed at baseline and after 3, 6, 12, and 24 months. At each visit, patients will fill out online questionnaires (~30 min) and are assessed by the RN, who calculates the DAS28 or DAPSA depending on the diagnosis. Study visits will take 30 minutes or less. The timeline and extensive data collection overview are shown in Figure 2 and Table 2. Data collection is the same for both the intervention group and the control group.

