**Figure 2. F2:**
[figure not shown]
Participant timeline.

**Table 2. T2:** Overview of data collection in intervention and control groups.

Data collection	T0	T3	T6	T12	T24
In-hospital evaluation					
Diagnosis: RA^a^ or PsA^b^	✓				
Check other inclusion and exclusion criteria	✓				
Informed consent	✓				
Demographic	✓				
History (fulfillment ACR^c^/and EULAR^d^ criteria for RA and PsA, disease duration, auto-antibody status, presence of erosions, DMARD^e^ history)	✓				
Comorbidity	✓				
Global assessment of disease activity by patient and RN^f^	✓	✓	✓	✓	✓
Adverse events (self-reported)		✓	✓	✓	✓
Hospital admission		✓	✓	✓	✓
Length, Weight, BMI, and waist circumference	✓	✓	✓	✓	✓
Physical examination by RN	✓	✓	✓	✓	✓
Online questionnaires					
General (smoking, alcohol, and drugs)	✓				
General health (VAS^g^)	✓	✓	✓	✓	✓
Pain (VAS)	✓	✓	✓	✓	✓
Morning stiffness (severity and duration; NRS^h^)	✓	✓	✓	✓	✓
Fatigue (VAS and FACIT-F^i^)	✓	✓	✓	✓	✓
HAQ^j^ (functional ability)	✓	✓	✓	✓	✓
EQ-5D-5L (quality of life)	✓	✓	✓	✓	✓
SF-36^k^ (quality of life)	✓			✓	✓
RAPID-3^l^	✓	✓	✓	✓	✓
Sleep (MOS-SS^m^)	✓	✓	✓	✓	✓
Perceived stress	✓	✓	✓	✓	✓
Physical activity	✓	✓	✓	✓	✓
Diet compliance	✓	✓	✓	✓	✓
WPAI^n^ (work and productivity)	✓	✓	✓	✓	✓
Medical consumption (MCQ^o^)	✓	✓	✓	✓	✓
Total time (min)	~34	~30	~30	~34	~34
Routine laboratory tests	✓	✓	✓	✓	✓

a RA: rheumatoid arthritis.

b PsA: psoriatic arthritis.

c ACR: American College of Rheumatology.

d EULAR: European Alliance of Associations for Rheumatology.

e DMARD: disease-modifying antirheumatic drug.

f RN: research nurse.

g VAS: Visual Analog Scale.

h NRS: Numeric Rating Scale.

i FACIT-F: Functional Assessment of Chronic Illness Therapy-Fatigue.

j HAQ: Health Assessment Questionnaire.

k SF-36: 36-item Short Form Health Survey.

l RAPID-3: Routine Assessment of Patient Index Data 3.

m MOS-SS: Medical Outcomes Study sleep scale.

n WPAI: Work Productivity and Activity Impairment.

o MCQ: Medical Consumption Questionnaire.

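### Four laboratory adverse events of special interest depend on unblinded reports by a route that Table 2 does not show, although laboratory tests are scheduled identically in both arms

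*Protocol article*

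**What the plan says.** The AEs section of the protocol article gives two routes for events of special interest: "AEs of special interest during the study will be collected at each study visit through patient questionnaires and/or physician reports". It then splits these events by source. The patient-reported group is infections and common complaints. The other group reads "Physician reported: infections, abnormal blood counts, abnormal liver function tests, decrease in kidney function, and increased cholesterol levels". The same section has a broader rule for adverse events in general: "All AEs reported spontaneously by the participant or observed by the investigator or research staff will be recorded".

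The Participant Timeline section describes what happens at a visit: "At each visit, patients will fill out online questionnaires (~30 min) and are assessed by the RN". It names no physician assessment, refers the reader to Figure 2 and Table 2 for the detail, and states that data collection does not differ between the arms. In Table 2 the one adverse-event row is labelled "Adverse events (self-reported" and is ticked at T3, T6, T12 and T24. Two other rows bear on safety: "Hospital admission" at the same four visits, and "Routine laboratory tests" at all five visits including T0.

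On masking, the Randomization and Blinding section says: "Patients, treating physicians, RNs, and researchers will know to which group patients are randomized".

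**The concern.** A patient can report diarrhoea or a headache but cannot be expected to report a fall in kidney function. Events of that kind need someone to look at a result, decide that it is abnormal, and record it. The AEs section assigns that task mainly to physicians, but the schedule has no place where a physician report is collected. Whoever does it knows which arm the patient is in.

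Treatment may also come to differ by arm. The section on concomitant care leaves tapering, continuation and intensification to the treating rheumatologist, and successful tapering is part of the primary end point. If the programme works as hoped, DMARD exposure will diverge, and attention to laboratory results, or readiness to call one an adverse event, could diverge with it. A difference between arms in reported laboratory events, or the absence of one, would then be hard to interpret.

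What is at stake is the safety statement. The article expects the health risk of the intervention to be low. Incomplete reporting would make that expectation look confirmed, while the trial may already hold evenly collected laboratory values that could test it.

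**Working it through.** No figure in the plan belongs to this point, so the check sets the sections side by side.

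1. **Which events are affected.** The physician-reported list has five items: infections, blood counts, liver tests, kidney function and cholesterol. The last four are laboratory findings, so 4 of 5.

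2. **Which routes the text provides.** The AEs section provides three: patient questionnaires, physician reports at each visit, and recording of events that the investigator or research staff observe. Only the second and third can realistically carry laboratory events.

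3. **Which routes the schedule provides.**

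| Source of safety information | AEs section | Table 2 |
|---|---|---|
| Patient self-report | yes | 1 row, 4 visits (T3, T6, T12, T24) |
| Physician report | yes, at each visit | no row |
| Observation by investigator or research staff | yes | no row |
| Hospital admission | as a criterion for a serious event | 1 row, 4 visits |
| Laboratory results | not named as a source | 1 row, 5 visits (T0 and the four above) |

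The text and the schedule agree on self-report. They do not agree on the physician route, which is the one named for the laboratory events. Where Table 2 names an assessor elsewhere, it is the patient or the research nurse.

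4. **Who is masked.** Treating physicians, research nurses and researchers all know the allocation. The masked group labels described in the Randomization and Blinding section apply during statistical analysis, after events have been recorded. They do not protect the recording step.

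5. **What is collected evenly.** The laboratory row applies to everyone at five visits, on the same schedule in both arms. A T0 result allows a later abnormality to be separated from one already present. The article does not list the analytes. The only ones it ties to the visits are the erythrocyte sedimentation rate and C-reactive protein, through the DAS28 and DAPSA formulas. Whether blood counts, liver tests, kidney function and cholesterol are in the panel cannot be settled from this document.

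6. **Size.** The article gives no event rate and no reporting rate, so a bias cannot be quantified and none is estimated here.

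**The case against.** The strongest case against has four parts.

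First, a reader might infer that a laboratory event enters the data only if an unblinded treating physician reports it. The AEs section does not support that. It also records events observed by the investigator or research staff, so a nurse or researcher who sees an abnormal scheduled result is covered. It speaks of physicians generally, not of treating physicians. This part stands in full.

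Second, Table 2 is presented as an overview, and a missing row there does not cancel a statement in the text that physician reports are collected at each visit. This stands in part. The omission does not show that the reports will not be collected. It does leave the article naming a source in one place and not scheduling it in another.

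Third, testing is scheduled equally, so closer watching of one arm is limited, and nothing in the document shows that staff will record the same result differently by arm. Open-label recording affects every adverse event in this trial. This also stands: uneven counting is a risk, not a demonstrated fault. The laboratory events differ from the others in that an objective, evenly scheduled source may already exist for them.

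Fourth, the analytes, cut-offs, adverse-event form and safety analysis are details that an article commonly leaves to the full protocol or analysis plan. Agreed, and their absence is not the point. The point is the mismatch between what is stated and what is scheduled, together with the choice of a judgement-based source.

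**Conclusion.** The point holds as a minor one. The AEs section and Table 2 do not match on how physician-reported events of special interest are collected, and 4 of the 5 items in that group are laboratory findings that self-report cannot supply. As described, these events depend on unblinded judgement by physicians, the investigator or research staff, through a route that the schedule does not show. Laboratory tests are meanwhile scheduled identically in both arms at T0, T3, T6, T12 and T24.

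A reader might go further and conclude that laboratory events will be missed, or that the safety comparison will be biased. The document does not establish either. Uneven reporting by arm is possible, and its size cannot be stated.

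The conclusion rests on two assumptions: that Figure 2, which could not be seen, shows no physician report at the visits, and that the routine panel contains at least some of the four kinds of test. If it contains none, the mismatch remains but deriving events from results is not available. The primary end point and the sample size are not affected.

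**What to change.** 1. Reconcile Table 2 with the AEs section: either add the physician and staff reports to the schedule, with the visits at which they are collected, or correct the text.

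2. For each analyte in the routine panel, derive new abnormalities at T3, T6, T12 and T24 from the scheduled results. Use one prespecified rule per analyte, the same in both arms, and define newness relative to the T0 result. This is a rule for counting events in the analysis. It is not guidance on managing patients, and no cut-off is proposed here.

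3. Report the derived abnormalities by arm, and keep physician and staff reports as a supplement.

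4. State which of the four kinds of laboratory event, if any, lie outside the panel and so rest on reports alone.

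The rule should be written down and dated before laboratory results are tabulated by arm. The Results section places the analysis after the last visit in May 2026, so this appears feasible. Because the article says the analysis plan has not changed since registration, the rule should be documented as an addition.

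The cost is a correction to the table or text, a short passage in the analysis plan and a small derivation. For analytes already in the panel it needs no new tests or visits. The downside is that some clinically trivial deviations will be counted, in both arms alike. Keeping the physician reports alongside lets the reader see which abnormalities were thought to matter.
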